# Rationale and design of ON-TRK: a novel prospective non-interventional study in patients with TRK fusion cancer treated with larotrectinib

**DOI:** 10.1186/s12885-022-09687-x

**Published:** 2022-06-07

**Keywords:** Larotrectinib, *NTRK* gene fusions, TRK fusion, Non-interventional study

## Abstract

**Background:**

Tropomyosin receptor kinase (TRK) fusion proteins resulting from neurotrophic tyrosine receptor kinase (*NTRK*) gene fusions are rare primary oncogenic drivers in a wide array of tumors. Larotrectinib is a first-in-class, highly selective, central nervous system-active TRK inhibitor approved by the US Food and Drug Administration (FDA), European Medicines Agency (EMA), and over 40 countries for the treatment of TRK fusion solid tumors in adult and pediatric patients. Due to the rarity of TRK fusion cancer, larotrectinib was granted accelerated approval based on a relatively small number of patients enrolled in three early phase trials. ON-TRK aims to evaluate the safety profile of larotrectinib in a broader population and over extended time periods.

**Methods:**

ON-TRK is a prospective, non-interventional, open-label, multicenter, multi-cohort, post-approval study in adult and pediatric patients with locally advanced or metastatic TRK fusion cancer treated with larotrectinib that will describe the safety and effectiveness of larotrectinib in real-world practice conditions. Adult patients will be grouped by tumor type and followed for at least 2 years. Patients < 18 years old will be enrolled under a ‘pediatric’ cohort regardless of tumor type and will be followed for 5 years to evaluate the risk of potential long-term adverse effects of larotrectinib on their growth and development. The effectiveness of larotrectinib in the overall study population as well as in patient subgroups will also be evaluated. Procedures avoided in patients with infantile fibrosarcoma (e.g., amputation) and the number of patients who were able to undergo surgery with a curative intent (excluding amputation) because of the use of larotrectinib will be described. Larotrectinib treatment patterns in real-world practice, including dosing and duration of treatment, will be described.

**Discussion:**

The FDA Accelerated Approval Program allows for earlier approval of and patient access to drugs that treat serious conditions and fill an unmet medical need. This study is designed to fulfill post-approval requirements set by the FDA as well as post-marketing requirements set forth by local regulatory bodies and is part of the risk management plan for the EMA.

**Study registration:**

This study is registered at ClinicalTrials.gov (NCT04142437).

**Protocol version:**

v2.5, 25 March 2021.

## Background

Tropomyosin receptor kinase (TRK) proteins are encoded by the neurotrophic tyrosine receptor kinase (*NTRK*) genes and mediate neurotrophin signaling, which is central to normal neuronal development and function [1, 2]. Activation of TRK receptors is initiated by the binding of neurotrophins, which causes autophosphorylation of specific tyrosine residues in the activation loop of the kinase domain. This autophosphorylation leads to the phosphorylation of additional tyrosine residues, which allows the docking of cytoplasmic adaptors and enzymes, in turn driving various downstream signaling pathways and subsequent physiological effects on cellular proliferation, growth, differentiation, and survival [2–5].

TRK fusion proteins are the product of *NTRK* gene fusions and have been identified as primary oncogenic drivers in a wide array of tumors [2, 6–8]. *NTRK* gene fusions occur when the 3′ region of the *NTRK* gene is joined with the 5′ end of a fusion partner gene through intra- or interchromosomal rearrangement. This *NTRK* gene fusion encodes a TRK fusion protein that contains the intact catalytic tyrosine kinase domain from the *NTRK* gene as well as one or more dimerization domains from the partner gene. The result is a TRK fusion protein that is constitutively activated, leading to uninterrupted downstream signaling messages that confer oncogenic potential [2, 9].

*NTRK* gene fusions are rare (occurring in < 1% of cancers) but are present in many types of adult and pediatric solid tumors. *NTRK* gene fusions occur more frequently in some rare tumors (e.g., secretory carcinoma of the salivary gland and infantile fibrosarcoma), and less frequently in other more common cancers (e.g., lung cancer and colorectal cancer) [10–13] (Table 1).

**Table 1 Tab1:** Prevalence of *NTRK* gene fusions in solid tumors

Tumor type	Prevalence	References
Appendiceal	0.56%–2%	Braghiroli et al. 2016 [36]; Forsythe et al. 2020 [37]
Cholangiocarcinoma	4%	Ross et al. 2014 [38]
Colorectal	0.2%–0.5%	Gatalica et al. 2019 [7]; Creancier et al. 2015 [39]; Forsythe et al. 2020 [37]
Glioblastoma	3%	Zheng et al. 2014 [40]
High-grade glioma	21.21%	Forsythe et al. 2020 [37]
High-grade glioma, pediatric	5.3%–6.19%	Forsythe et al. 2020 [37]; Okamura et al. 2018 [41]
Head and neck cancer	0.5%	Stransky et al. 2014 [12]
Infantile fibrosarcoma	70%–91%	Amatu et al. 2019 [2]; Vaishnavi et al. 2015 [9]; Forsythe et al. 2020 [37]
Low-grade glioma	0.4%–0.88%	Stransky et al. 2014 [12]; Forsythe et al. 2020 [37]
Low-grade glioma, pediatric	1.61%	Forsythe et al. 2020 [37]
Lung adenocarcinoma	0.1%	Gatalica et al. 2019 [7]; Farago et al. 2015 [42]; Forsythe et al. 2020 [37]
Melanoma	0.3%	Stransky et al. 2014 [12]; Forsythe et al. 2020 [37]
Papillary thyroid carcinoma	< 5%–25%	Brzezianska et al. 2006 [43]; Greco et al. 2010 [44]; Wajjwalku et al. 1992 [45]; Said et al. 1994 [46]; Butti 1995 [47]; Delvincourt et al. 1996 [48]; Bounacer et al. 2000 [49]; Forsythe et al. 2020 [37]
Pilocytic astrocytoma	3%	Jones et al. 2013 [50]
Secretory breast carcinoma	92.87%	Tognon et al. 2002 [51]; Forsythe et al. 2020 [37]
Secretory carcinoma of salivary gland	66%–93%	Skalova et al. 2014 [52]; Skalova et al. 2010 [53]; Forsythe et al. 2020 [37]
Soft tissue sarcoma (non-infantile fibrosarcoma)	< 5%	Demetri et al. 2020 [55]
Spitzoid melanoma	16%	Wiesner et al. 2014 [54]

Testing for *NTRK* gene fusions should be considered part of the standard diagnostic work-up for solid tumors in order to optimize treatment, as there are approved small-molecule inhibitors with activity against TRK fusion cancer [14, 15]. Fluorescence in situ hybridization (FISH), reverse-transcription polymerase chain reaction (RT-PCR), or next-generation sequencing (NGS) are the recommended testing methods to detect the presence of an *NTRK* gene fusion [16, 17]. While pan-TRK immunohistochemistry (IHC) is more cost- and resource-efficient than these molecular testing methods, a positive IHC test is insufficient to confirm a diagnosis of TRK fusion cancer. Moreover, cancers involving tissues with endogenous basal wild-type TRK protein expression, such as central nervous system (CNS), endocrine, and smooth muscle tumors, can produce false positive results. Therefore, it is necessary to confirm any positive IHC results with molecular testing [18, 19]. Given the relatively small number of pediatric patients with cancer as compared with adult patients, it may be feasible for pediatric patients to undergo molecular testing upon diagnosis, particularly with tumor types that are known to harbor *NTRK* gene fusions. For instance, the *ETV6-NTRK3* gene fusion is pathognomonic for infantile fibrosarcoma and is routinely detected by break-apart FISH at diagnosis [19].

Larotrectinib is a first-in-class, highly selective, CNS-active oral TRK inhibitor with low nanomolar potency against all three TRK family members (TRKA, TRKB, and TRKC) [6]. Larotrectinib potently inhibits adenosine triphosphate binding to the TRKA, TRKB, and TRKC catalytic domains, while showing low binding affinity for other tyrosine kinases [13, 20]. A primary safety and efficacy analysis used pooled data from the first 55 patients with advanced progressive cancers harboring *NTRK* gene fusions who enrolled in three phase I and II trials (NCT02122913, NCT02637687, and NCT02576431), with 17 unique cancer diagnoses included. The objective response rate (ORR) assessed by an independent review committee (IRC) was 75% (complete response rate of 13%). Efficacy was observed regardless of tumor type or patient age, *NTRK* gene, or fusion partner. At 1 year, 71% of responses were ongoing and 55% of patients remained free of progression. In this primary analysis population, larotrectinib demonstrated a low frequency of clinically significant adverse events (AEs) in both adult and pediatric patients with TRK fusion cancer; 93% of AEs reported were grade 1–2. The most common grade 3–4 AEs were anemia (11%), increased aspartate aminotransferase or alanine aminotransferase (7%), weight increase (7%), and decreased neutrophil count (7%). No grade 3 treatment-related AEs occurred in more than 5% of the patients and there were no grade 4–5 treatment-related AEs [21]. Based on these phase I/II data, larotrectinib became the first tyrosine kinase inhibitor approved by the US Food and Drug Administration (FDA) for tumor-agnostic use in both adult and pediatric patients with advanced TRK fusion solid tumors. It became the first drug granted tumor-agnostic approval by the European Medicines Agency (EMA) and is now approved in over 40 countries for tumor-agnostic use in patients of all ages with TRK fusion cancer [22, 23]. In subsequent data cuts with longer follow-up, overall tumor responses were consistent and safety profiles were comparable with previous reports, demonstrating the durability and long-term safety of larotrectinib [24].

Efficacy of neoadjuvant larotrectinib therapy has also been demonstrated in situations in which the patient would otherwise be subjected to amputations or disfiguring surgeries. Five children with locally advanced TRK fusion sarcomas achieved a partial response and underwent surgical resection after a median of six treatment cycles. Based on institutional pathologic assessment, surgical resections were R0 (negative resection margins with no tumor at the inked resection margin) in three patients, R1 (microscopic residual tumor at the resection margin) in one patient, and R2 (macroscopic residual tumor at the resection margin) in one patient. Three patients achieved complete or near-complete pathological responses and at last follow-up remained disease free 7–15 months after surgery [25, 26].

In an integrated dataset of 159 patients with non-CNS TRK fusion cancer, larotrectinib demonstrated durable efficacy and a favorable long-term safety profile [24]. The most common tumor types in the integrated dataset included soft tissue sarcoma (43%, including infantile fibrosarcoma and gastrointestinal stromal tumor), thyroid cancer (16%), salivary gland cancer (13%), and lung cancer (8%). Larotrectinib showed efficacy regardless of tumor type, with an investigator-assessed ORR of 79%. Median duration of response (DOR) was 35.2 months. Median progression-free survival (PFS) was 28.3 months, and median overall survival (OS) was 44.4 months [24].

No new safety signals for larotrectinib were identified in the expanded safety population (*n* = 260). AEs were primarily of grade 1–2, and the pattern and frequency were similar across age groups. The most frequently occurring AEs of any grade were fatigue (33%), increased alanine aminotransferase (28%), and cough (28%). Grade 3–4 larotrectinib-related AEs were reported in 13% and 1% of patients, respectively. The most common were increased alanine aminotransferase (3%), anemia (2%), and decreased neutrophil count (2%) [24].

Patient-reported outcomes also showed improvement in patients treated with larotrectinib; rapid, sustained, and clinically meaningful improvements in quality of life were observed in the majority of patients [27]. Larotrectinib has also demonstrated intracranial activity in patients with primary CNS tumors [28] or non-CNS solid tumors with brain metastases [24].

Results from these clinical trials demonstrated that in addition to having tumor-agnostic activity, larotrectinib is also effective across age groups, including in children and adolescents. Of the 159 patients analyzed in the integrated dataset, 52 (33%) were aged < 18 years old [29]. Tumor types included infantile fibrosarcoma (56%), other soft tissue sarcoma (37%), thyroid (4%), congenital mesoblastic nephroma (2%), and melanoma (2%). ORR was 92%; at the time of data analysis, medians for DOR, PFS, and OS were not reached. With the duration of treatment ranging from 1.3 + to 34.0 + months, larotrectinib was well tolerated with low rates of discontinuation due to treatment-related AEs and low rates of neurologic AEs.

Longer-term safety evaluation is required, and this is particularly relevant for pediatric patients in order to investigate potential developmental effects of treatment. There are limited available data on the safety profile of larotrectinib in a broader population and over a longer time period. Real-world safety and effectiveness data in a larger patient population are needed with a longer-term follow-up. The ON-TRK study is a prospective, open-label, multicenter, multi-cohort, non-interventional study in patients with locally advanced or metastatic TRK fusion cancer treated with larotrectinib. The aim of the ON-TRK study is to describe the safety and effectiveness of larotrectinib in this patient population under real-world conditions in standard clinical practice. As it is a post-approval safety study, it is also designed to fulfill FDA requirements for the accelerated approval of larotrectinib, which include additional studies to validate and describe the clinical benefits of larotrectinib. Post-approval commitments set forth in the FDA’s accelerated approval of larotrectinib require enough pediatric patients be followed for 5 years to evaluate the risk of potential long-term adverse effects of larotrectinib on growth and development and the assessment of unexpected risks of serious AEs (SAEs) in patients requiring a third larotrectinib dose modification due to toxicity [30]. This study is also intended to fulfill the post-marketing requirements set forth by the regulatory bodies of Canada and South Korea, and is part of the risk management plan provided to the EMA [31].

## Methods

### Study overview

ON-TRK is an international, prospective, open-label, multicenter, multi-cohort, non-interventional study. The guidelines on good pharmacovigilance practices (GVP module VI [32] and GVP module VIII [33, 34]) will be followed. Before documentation of any patient data, informed consent will be obtained from the patient, parent/legal guardian, or legal representative. The study is registered on ClinicalTrials.gov (NCT04142437).

### Study design

#### Participants

Inclusion criteria include adult and pediatric (< 18 years old) patients with locally advanced or metastatic solid tumors with an *NTRK* gene fusion for whom a decision to treat with larotrectinib has been made before enrollment in the study (Fig. 1). Patients with prior TRK inhibitor therapy and patients with *NTRK* genomic alterations other than fusions (such as amplifications or point mutations) will be excluded.

**Fig. 1 Fig1:**
[figure not shown]
Study design. *NTRK* neurotrophic tyrosine receptor kinase, *TRK* tropomyosin receptor kinase

*NTRK* gene fusions will be detected locally by NGS, FISH, RT-PCR, or any other genomic test able to detect *NTRK* gene fusions. Cohorts will be defined by the tumor types of enrolled adult patients, including gastrointestinal, head and neck, lung, soft tissue sarcoma, primary CNS, melanoma, or ‘other’. All pediatric patients, regardless of tumor type, will be enrolled within a ‘pediatric’ cohort. Per the study protocol, central pathological review is not planned; all pathology data will be collated locally at each study site. The decision on the dose and duration of treatment is solely at the discretion of the treating physician, based on the recommendations included in the local product information. Examinations and the laboratory monitoring schedule will follow local label recommendations in line with local standard of care.

### Objectives

The study objectives and associated variables are listed in Table 2. Up to 300 patients with *NTRK* gene fusion cancer will be included in this analysis. As the primary objective of this study is to describe the incidence of treatment-emergent AEs (TEAEs) in a real-world setting, the rationale for this study size was based on the probability of observing at least one TEAE event for a range of true incidence rates, including some of the uncommon events. For a true event incidence of 1% and a sample size of 300 patients, the probability of observing at least one event is 95%. Therefore, a total of approximately 300 patients was considered sufficient to observe at least one AE for even uncommon events.

**Table 2 Tab2:** Study objectives and variables

Objective	Variables
**Primary**: safety of larotrectinib in adult and pediatric patients with locally advanced or metastatic TRK fusion cancer	TEAEs in real-world practice conditions • Incidence • Severity • Seriousness • Outcome • Causality assessment (ARs)
**Secondary**: • Effectiveness of larotrectinib as per investigator assessment in the total study population as well as in patient subgroups (including, but not limited to, age, *NTRK* gene, *NTRK* gene fusion partner, testing methodology, country/region, and prior therapy [type and/or number of lines of therapy])	• Patient demographic and baseline characteristics • Disease history (including pathology report at baseline and subsequently as applicable) • Comorbidities • Method for detecting *NTRK* gene fusion (including testing report at baseline and subsequently as applicable) • ECOG, Lansky, or Karnofsky performance status • Tumor assessments (ORR, DCR, DOR, TTR, PFS, OS) per investigator assessment • Date of radiologic or clinical progression on larotrectinib
• Larotrectinib treatment patterns	• Larotrectinib use (initiation and termination dates, dosage, and dose modification)
• Long-term effects of larotrectinib on growth, developmental milestones, and sexual development in the pediatric cohort • Long-term effects of larotrectinib on neurologic outcomes in all patients	• Developmental milestones; age at adrenarche or menarche (if applicable); Tanner scale • Neurological examination
	• Laboratory examination data; and date of death/last follow-up
**Exploratory:** • Effectiveness of larotrectinib	• Tumor assessments (ORR, DCR, DOR, TTR, PFS, OS) based on radiologic assessments of tumor response per IRC, as applicable
• Procedures avoided because of the use of larotrectinib (e.g., amputation or other disfiguring procedures) in patients with infantile fibrosarcoma	• Whether an amputation was considered for the patient prior to treatment with larotrectinib (e.g., in patients with infantile fibrosarcoma)
• Number of patients who underwent surgery with a curative intent (excluding amputation) because of the use of larotrectinib	• Surgery (with curative intent) while on larotrectinib
• Description of systemic treatments prior to larotrectinib therapy	• Previous systemic therapy (initiation and termination dates, doses, duration of treatment, best tumor response to therapy, date of radiological progression on therapy, reasons for discontinuation)

*AR* Adverse Reaction, *DCR* Disease Control Rate, *DOR* Duration of Response, *ECOG* Eastern Cooperative Oncology Group, *IRC* Independent Review Committee, *NTRK* Neurotrophic Tyrosine Receptor Kinase, *ORR* Objective Response Rate, *OS* Overall Survival, *PFS* Progression-free Survival, *TEAE* Treatment-emergent Adverse Event, *TRK* Tropomyosin Receptor Kinase, *TTR* Time To Response

Secondary objectives include describing the effectiveness of larotrectinib by local investigator assessment, including by subgroups of patients (e.g., age, *NTRK* gene, *NTRK* gene partner, testing methodology, country/region, prior therapy), patterns of larotrectinib treatment, long-term effects of larotrectinib on growth, developmental milestones, and sexual development of the pediatric cohort, and long-term effects of larotrectinib on neurologic outcomes for all patients (Table 2).

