#### Analysis of exploratory variables

Effectiveness variables, including ORR, DCR, DOR, TTR, and PFS, will also be determined by an IRC, based on radiological assessments of tumor response as applicable. These effectiveness variables will be determined by an IRC for patients who have technically adequate baseline and on-treatment radiological assessments of tumor response that have been centrally collected at the imaging core laboratory. In patients who had systemic anti-cancer therapy prior to the study, the treatment data will be summarized descriptively. Dosing of other treatment used prior to the study, including start/stop date, duration of treatment, given doses, reasons for discontinuation, and time from discontinuation of treatment to start of larotrectinib, will be retrospectively collected and summarized descriptively in the total study population. For patients with infantile fibrosarcoma, the number and percentage of patients who avoided amputation will be reported. The number and percentage of patients who underwent a surgery for a curative intent while being treated with larotrectinib (excluding amputation) will also be presented. In addition, local protocol amendments may be requested. For example, patient-reported outcomes data will be collected in Austria, Germany, and Canada.

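### The curative-surgery objective is worded as enablement by larotrectinib, but its variable and analysis count all curative-intent surgery on treatment, including in patients who were already operable

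*Protocol article*

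**What the plan says.** The Abstract (Methods) announces that "the number of patients who were able to undergo surgery with a curative intent (excluding amputation) because of the use of larotrectinib will be described". Table 2 in the Objectives section repeats the attribution as an exploratory objective: "Number of patients who underwent surgery with a curative intent (excluding amputation) because of the use of larotrectinib".

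The variable set against that objective in Table 2 is "Surgery (with curative intent) while on larotrectinib". The section on analysis of exploratory variables then states: "The number and percentage of patients who underwent a surgery for a curative intent while being treated with larotrectinib (excluding amputation) will also be presented".

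The neighboring exploratory objective, on procedures avoided, does have a pre-treatment variable: "Whether an amputation was considered for the patient prior to treatment with larotrectinib". Table 2 gives infantile fibrosarcoma as an example for that item, not as a limit on it.

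The Participants section admits "patients with locally advanced or metastatic solid tumors with an *NTRK* gene fusion for whom a decision to treat with larotrectinib has been made". It lists no condition that the disease be unresectable.

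**The concern.** The objective asks how many patients reached curative surgery through the drug. That is a statement about what would have happened without it. The listed variable and analysis record only that surgery took place during treatment. Someone with an operable tumor who has a course of larotrectinib and then a resection that was feasible all along is counted exactly like someone converted from unresectable disease.

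The design offers no other route to attribution. The study is non-interventional and descriptive, and no comparator is described. The patient's surgical status before the first dose is the only practical basis for an enablement statement. The objective is featured in the Abstract, and the Discussion says the study is meant to support conversion from accelerated to full approval, so the resulting count may well be read as evidence of benefit.

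**Working it through.** **The plan's own figures.** The article gives no figure for this objective. Its only planning figure is the 95% probability of seeing at least one event with 300 patients and a true incidence of 1%. It reproduces, 1 − 0.99^300 = 0.951, but has no bearing on surgery.

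**Objective, variable and analysis side by side.**

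| Element | Place in the article | What it fixes |
|---|---|---|
| Objective | Abstract (Methods); Table 2 | Surgery made possible by the drug |
| Variable | Table 2 | Surgery during treatment (timing only) |
| Analysis | Analysis of exploratory variables | Number and percentage with surgery during treatment; no condition on prior operability |
| Entry | Participants | Locally advanced or metastatic; unresectability not required |
| Neighboring objective | Table 2 | Has a pre-treatment item (amputation considered) |

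1. For the count to answer the objective, every patient in it must have lacked an acceptable curative operation before treatment.
2. Entry does not ensure this. Locally advanced disease is admitted without a resectability condition, and treatment duration is left to the physician, so a preoperative course is possible. The Background describes such use: five children had resection after a median of six cycles.
3. The listed variable and analysis do not ensure it either, since both depend on timing alone.
4. Hence already operable patients can enter the numerator.

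**Illustration of size (all rates assumed).** Let N = 300, r = share resectable at baseline, s_r = probability of curative surgery on treatment if resectable, s_u = the same if not.

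- Surgeries counted = N[r·s_r + (1 − r)·s_u]
- Of these, in patients not resectable at baseline = N(1 − r)·s_u
- Share in already resectable patients = r·s_r / [r·s_r + (1 − r)·s_u]

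| r | s_r | s_u | Counted | Not resectable at baseline | Share already resectable |
|---|---|---|---|---|---|
| 0 | any | 0.10 | 30.0 | 30.0 | 0% |
| 0.05 | 0.30 | 0.10 | 33.0 | 28.5 | 4.5/33.0 = 14% |
| 0.10 | 0.30 | 0.10 | 36.0 | 27.0 | 9.0/36.0 = 25% |
| 0.30 | 0.60 | 0.05 | 64.5 | 10.5 | 54.0/64.5 = 84% |

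The second and fourth rows are the extremes over r from 0.05 to 0.30, s_r of 0.30 or 0.60, and s_u of 0.05 or 0.10. The spread shows how strongly the answer depends on a quantity that the stated analysis does not use.

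**The case against.** **The article condenses a fuller protocol.** A reader might infer that baseline resectability is recorded nowhere. The article does not support that. The case report form is not shown, and the baseline entries in Table 2, such as "Disease history (including pathology report at baseline and subsequently as applicable", are not itemized and could contain it. This objection stands against any claim about data capture. It does not remove the mismatch, because the variable and analysis stated for this objective make no use of such information.

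**Part of the baseline information is already listed.** Prior consideration of amputation is collected and is not confined to infantile fibrosarcoma. That stands, and the fix should build on it. The item does not identify tumors that were unresectable, or resectable only by disfiguring surgery other than amputation.

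**The analysis sentence is neutral.** It speaks of surgery during treatment, and the article calls all analyses explorative and descriptive. A reader might infer that the plan itself credits each operation to the drug. It does not; the over-attribution arises when the neutral count is reported as the result for the objective. Since objective and variable share a row of Table 2, that is the natural reading.

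**The denominator.** A reader might also infer that the percentage is diluted by patients with widespread metastases. The article states no denominator for this percentage, so that cannot be shown, and the objective itself is a number of patients, which cannot be diluted.

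**The error may be small.** The Background presents neoadjuvant use in patients who otherwise faced amputation or disfiguring surgery, so few enrolled patients may be operable from the start. The article does not settle this either way.

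**Importance.** This is one descriptive line among the exploratory objectives. That stands and limits the weight of the point.

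**Conclusion.** The point holds as a mismatch between a stated objective and its stated measure. The objective claims that the drug made surgery possible; the variable and analysis count all curative-intent surgery on treatment. Because entry does not require unresectable disease, patients whose resection was already feasible would count toward the result.

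The size cannot be computed from the article. The 14% to 84% range rests wholly on assumed resectability and surgery rates, and the error is zero if no enrolled patient was resectable at baseline. The primary safety objective, the secondary effectiveness analyses and the sample size are unaffected. The conclusion rests on the variables and analysis that the article lists, not on any claim about what the full case report form contains.

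**What to change.** Record resectability before larotrectinib starts, taken from existing physician or tumor-board notes and using the amputation item already listed. Three levels suffice:

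- (a) resectable with acceptable function;
- (b) resectable only by amputation or disfiguring surgery;
- (c) unresectable.

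Report curative resections (excluding amputation) in groups (b) and (c) as the figure for the objective. Report resections in group (a) separately, and keep the all-patient count as description. If the full case report form already holds this information, only the table needs to change.

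If the item cannot be collected, reword the objective to surgery with curative intent while on larotrectinib, and make no enablement claim. That needs no new data.

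The cost is one case report form item, one revised table and a smaller headline count. Patients already enrolled (22 as of November 2021, under Current study status) would need retrospective abstraction. That should be flagged in the report, because the rating is a judgment and may be made after the surgical outcome is known. Even with the item, an uncontrolled study does not prove that the drug caused the surgery; the change removes the patients for whom the claim plainly fails.
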